*What (procedure)*	Individual support during the RTW-process is provided according to the four-phase model of vocational reintegration (*Co-orientation, Coordination, Cooperation, Re-co-orientation*) [16]. The process of RTW is discussed, prepared, and followed up in detail according to the phases. In some cases, the IG-TP may contact the company doctor (e.g. via phone) and accompany RTW meetings with the employer.	Aftercare group during the RTW process is provided according to the IGLOO model [18]. The treatment focuses on promoting resources, including individual resources (e.g. stress detection and management techniques, interpersonal skills at work), as well as on using the provided organisational and group-level resources to enhance working conditions. Mindfulness practices are provided at the start of every session via an e-mental health platform [71].	The web-based aftercare is provided on an e-mental health platform [71] and is aligned in concept and content with Modules A and B (e.g. stress management and mindfulness practices). It consists of 8 different thematic blocks. After the entry into a particular block that is coordinated by the IG-TP, participants can choose blocks according to personal preferences. This aftercare follows a blended-care approach, in which up to 3 video call sessions can be arranged.
*Who provides*	Each study centre consists of a multidisciplinary RTW-PIA treatment team (e.g. psychotherapists, psychiatrists, occupational therapists, social workers). The IG-TP should ensure continuity of treatment throughout Modules A-C.		
*How*	It consists of face-to-face individual sessions between the participant and IG-TP, and follows a needs-oriented approach. Thus, the delivered treatment by the IG-TP is less standardised.	It consists of monthly face-to-face group sessions, consisting of 3–9 people. IG-TP have a motivating, resource-oriented attitude. The treatment delivered is to some extent manualised and serves as orientation/guidance.	It combines therapy elements, free text journaling, video calls and psycho-educational information. At the end of each block, IG-TP will give asynchronous (written) feedback. Module C follows a needs-oriented approach for which a written procedure was jointly agreed.

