### *Allocation and blinding*

Patients will be randomly assigned to either IG or CG with a 1:1 allocation, using permuted block randomisation with varying sizes stratified by study centre. Before recruitment began, five randomisation lists were prepared via an online randomisation service [72] by an independent researcher, blinded to the study conditions. For adequate allocation concealment, the generated lists were then securely transferred to an independent administrative working group, to which the evaluators, clinical practitioners, and participants never have access during recruitment. The baseline assessment takes place before group allocation to minimise reporting and selection bias. After completion, all participants will be randomised according to their chronological order of survey participation. The respective randomisation date will serve as the participant´s admission to the study. Blinding among study participants and treatment providers will not be possible before, during, or after the study. Due to the questionnaire design with items concerning the individual intervention modules, the evaluators will also not be blinded.

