#### Sample size and power calculation

In order to demonstrate a 15% increase in the proportion of employees from the IG achieving SRTW, based on [80] (CAU: 60%; RTW-PIA: 75%; power: 80%; significance level: 5%), the required sample size will be a minimum of 152 study participants per study arm. Calculations were performed with a sample size software [98]. Following previous authors [58, 99], we assumed a drop-out rate of 40%; thus, 506 participants will be needed in total.

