#### *Statistical analyses*

### Effectiveness evaluation

The primary outcome will be analysed using a logistic regression model to determine the odds ratio of the intervention effect. First, we will estimate a baseline model including treatment group (IG vs. CG) as a dummy-coded predictor variable and SRTW achievement as the outcome variable. Second, we will compute an adjusted estimate by including the stratification variable of the study centres as well as, if necessary, other socio-demographic variables for which differences between IG and CG occurred despite randomisation. Weighted effect coding will be considered for study centre, using the largest group as the reference group. Third, we will explore interaction effects between treatment group and all baseline assessments of the secondary outcomes and further variables. In case of statistically significant interaction effects, we will report intervention effects for different values of the covariates. In these and subsequent models, we will adopt a significance level of 5% for testing the focal parameters and report corresponding 95% confidence intervals (CIs).

In the context of the secondary analysis, multiple-group latent growth curve models (LGCM) will be estimated to investigate the effect of the intervention on changes in health-related quality of life, mental functioning, overall job satisfaction, severity of mental illness and work ability. LGCM are based on a structural equation modelling framework and allow for a more flexible adaptation to the specifics of the data structure than many multilevel models [100]. For each secondary outcome variable, we will include data at five time points and estimate a multiple group latent-basis model. This model is a less restrictive variant of the linear growth curve model, i.e. it contains a latent intercept for baseline differences and a latent slope for change differences, but can also represent nonlinear forms of change. If necessary, we will allow the residual variances to differ between treatment groups and time points. The focal parameter in each model is the mean difference of the latent slopes between treatment groups.

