### Health-economic evaluation

Missing cost and effect data will be imputed, using MICE. Two multilevel models will be specified, one for costs and one for effects, which consider the hierarchical structure of the data [105]. For effects, normal-based 95% CIs will be estimated. For the costs, 95% CIs will be estimated using bias-corrected and accelerated bootstrapping with 2,000 replications [106]. For this, cluster bootstrapping will be used, which is recommended for resampling hierarchical data [107]. The incremental cost-effectiveness ratio will be estimated by calculating the difference in costs between treatment groups divided by the difference in effectiveness of the treatment groups. The joint uncertainty surrounding costs and effects will be summarised using cost-effectiveness planes and cost-effectiveness acceptability curves [108]. To test the robustness of the base-case findings, probabilistic sensitivity analyses will be done by changing several assumptions made in the base-case scenario (e.g. about unit costs and volumes). The health-economic evaluation will be conducted using Stata.

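### The primary logistic model and the sample size make no stated allowance for outcome correlation within Module B groups or RTW-PIA providers; if that correlation is above zero, the standard error is too small and power is below 80%

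*Protocol article*

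**What the plan says.** **Primary model.** The statistical analysis section (Effectiveness evaluation) describes a logistic regression that begins with "a baseline model including treatment group (IG vs. CG) as a dummy-coded predictor variable". A second step adds study centre and, if needed, socio-demographic variables that differ between arms. For these models, "we will adopt a significance level of 5% for testing the focal parameters and report corresponding 95% confidence intervals (CIs"). The listed sensitivity analyses are two per-protocol subsets and a split by diagnosis. The robust standard errors mentioned there deal with non-normality in the secondary growth models.

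**Sample size.** The inputs are "CAU: 60%; RTW-PIA: 75%; power: 80%; significance level: 5"%, and "the required sample size will be a minimum of 152 study participants per study arm". Then "we assumed a drop-out rate of 40%; thus, 506 participants will be needed in total". No ICC or design effect is given.

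**Randomisation and delivery.** Individuals are allocated "using permuted block randomisation with varying sizes stratified by study centre". Of Module B, Table 1 says: "It consists of monthly face-to-face group sessions, consisting of 3–9 people". It schedules 6–9 meetings in the first 12 months and names support among members and group cohesion as the route to benefit. Table 1 also intends one provider to follow a participant through all three modules. The Interventions section says that the RTW-PIA teams do not carry out usual care.

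**Economic analysis.** Sustainable return to work (yes/no) is the effect in the cost-effectiveness analysis. Costs and effects each get a multilevel model, "which consider the hierarchical structure of the data". The level of that hierarchy is not named.

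**The concern.** The trial randomises individuals but treats one arm in groups. If members of a Module B group influence one another, as the module intends, or if providers differ in skill, outcomes in the intervention arm are positively correlated within groups or providers. Module B and the RTW-PIA teams have no counterpart in the control arm. A study-centre term common to both arms removes differences between centres, but not correlation within a centre that arises in one arm.

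An analysis that treats all participants as independent would then give a confidence interval for the odds ratio that is too narrow and a test that rejects more often than 5%. The planned numbers would also deliver less than 80% power. The error leans towards a false positive, in a trial whose positive result could support adoption into standard care.

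The protocol is also uneven on this point. The same binary outcome is analysed with a multilevel model in the economic evaluation and without one in the primary analysis.

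**Working it through.** **1. Reproduce the plan's figure.** Inputs from the sample-size section: control 60%, intervention 75%, power 80%, significance level 5%. Sidedness is not stated there and is taken as two-sided: this gives 152, whereas one-sided gives 120. With mean proportion 0.675 and no continuity correction:

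n = [1.96·√(2·0.675·0.325) + 0.8416·√(0.60·0.40 + 0.75·0.25)]² / 0.15²
= (1.2982 + 0.5503)² / 0.0225 = 151.9, so 152 per arm.

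Allowing for drop-out, 304/0.6 = 506.7, in line with the stated 506. The figure reproduces as a calculation with independent participants, that is, with ICC = 0.

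**2. Add clustering in the intervention arm.** Two assumptions are needed that the protocol does not supply: the ICC, and no clustering in the control arm. With m analysed members per group, the intervention-arm variance is multiplied by

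DE = 1 + (m − 1)·ICC.

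With 152 analysed per arm:
- Type I error of the analysis that ignores clustering: 2·[1 − Φ(1.96·√(2/(1 + DE)))].
- Power of a test that uses the correct standard error: Φ[(0.15 − 1.96·SE₀)/SE₁], where SE₀ = √(0.675·0.325·(1 + DE)/152) and SE₁ = √((0.24 + 0.1875·DE)/152).

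Worked case, m = 9 and ICC 0.05: DE = 1.40. Type I error is 2·[1 − Φ(1.789)] = 7.4%. SE₀ = 0.0589 and SE₁ = 0.0575, so power is Φ(0.603) = 72.7%.

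**3. Results if every group member is analysed.**

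| m | ICC | DE | Type I error | Power |
|---|---|---|---|---|
| 3 | 0.01 | 1.02 | 5.1% | 79.7% |
| 3 | 0.05 | 1.10 | 5.6% | 78.1% |
| 6 | 0.01 | 1.05 | 5.3% | 79.1% |
| 6 | 0.05 | 1.25 | 6.5% | 75.4% |
| 9 | 0.01 | 1.08 | 5.5% | 78.5% |
| 9 | 0.05 | 1.40 | 7.4% | 72.7% |

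At ICC 0.05 the naive standard error is about 2% (m = 3) to 8% (m = 9) too small. A simulation of the naive logistic test with correlated binary outcomes gave similar rejection rates under no effect at ICC 0.05: 6.7% for m = 6 and 7.7% for m = 9.

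**4. Allow for the planned drop-out.** The 3–9 are people in a group, not people with outcome data. If 40% are lost evenly, 0.6·3 = 1.8 to 0.6·9 = 5.4 members per group are analysed. At ICC 0.05:
- m = 1.8: DE = 1.04, type I error 5.2%, power 79.3%.
- m = 5.4: DE = 1.22, type I error 6.3%, power 75.9%.

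**5. Provider as the cluster.** The protocol gives no caseload. With an assumed 15–25 analysed participants per provider, power is 77.4–75.5% at ICC 0.01 and 67.6–60.1% at ICC 0.05.

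**The case against.** **The effect is conditional.** A reader might infer that the primary standard error is too small and that the 80% is overstated as matters of fact. The protocol does not support that. It reports no ICC, and at ICC 0.01 the group-level loss of power is under 2 percentage points for every group size from 3 to 9. This objection stands, and the point is worded accordingly.

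**The control arm may be clustered too.** The description of usual care lists group therapy and appointments with shared staff, and both arms receive usual care. A cluster-free control arm is therefore an assumption, and treating each control participant as a cluster of one is not established. What is specific to the intervention arm is Module B and the RTW-PIA team. This also stands.

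**The contrast with the economic models is limited.** Their hierarchy may be study centre, which the primary analysis includes in its second step. A reader might infer that the economic models already handle Module B groups; nothing in the protocol says so. What remains is that one outcome is modelled with a hierarchy in one place and without one in the other.

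**Groups may be open.** The protocol does not say that membership is fixed, so one group label per participant may not exist. This affects the choice of method, not the need for one.

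**Such details belong in the analysis plan.** The protocol defers further details to a plan to be pre-registered before database closure, which is not shown and may add a cluster term. That is fair for the model, and absence of the term from the article is not in itself an error. It does not answer the power statement, which is fixed here without any allowance.

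**Conclusion.** The point holds in conditional form. The 152 and 506 are arithmetically sound, but they rest on independent outcomes, and the stated primary and sensitivity analyses do not examine that assumption, although one arm is treated in groups by its own teams.

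On the assumptions of ICC 0.05, 152 analysed per arm and no control-arm clustering, the group-level effect is moderate: a few points of power and roughly one-half to two and a half points of type I error across 3–9 analysed members, and less once even drop-out is allowed for. It is negligible at ICC 0.01. Provider clusters, if larger than groups, would matter more at the same ICC, but their size is not in the protocol. The documents do not show which of these cases applies, so the result should be accompanied by an analysis that can tell.

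**What to change.** 1. **Record the clusters.** Add Module B group attendance, by session, and the main RTW-PIA provider to the existing participant-related documentation sheet. Table 3 lists number, date and duration of sessions for it, but no group or provider identifier.
2. **Pre-specify a companion analysis**, at the least, to be reported beside the primary result: a logistic analysis that allows for intervention-arm clustering, through a partially nested random effect or cluster-robust standard errors with a small-sample correction. Cluster on provider, or use a multiple-membership structure if groups are open. Examine control-arm clustering where usual-care groups or providers are shared.
3. **Qualify the power statement.** Say that 80% assumes ICC = 0, and give power over a range such as ICC 0–0.05.
4. **Name the level** of the hierarchy in the economic models, so that the two analyses of the same outcome can be compared.

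The analysis plan is still to be registered before database closure, so there is a place for this. The cost is a little more data recording, a slightly wider confidence interval and a less favourable power statement. No extra patients are needed.

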### Further variables

The following variables will be predominantly used as possible outcomes, covariates, moderators, or mediators within further exploratory analyses.

***Depressive symptoms*** will be measured with the Patient Health Questionnaire (PHQ-9) [87]. The PHQ-9 has a 4-point response scale, ranging from 0 (*not at all)* to 3 (*nearly every day*). The sum score ranges from 0 to 27, with higher scores indicating the severity of depressive symptoms.

***Interpersonal trust*** will be measured with the Interpersonal Trust Short Scale (KUSIV3) [88]. The KUSIV3 has a 5-point response scale, ranging from 1 (*do not agree at all*) to 5 (*completely agree*). The sum score ranges from 3 to 15, with higher scores indicating higher interpersonal trust.

***RTW expectation*** will be assessed with a single-item from the Screening Instrument Work and Occupation (SIBAR) [89]. The question was slightly adapted with respect to the study-specific setting at baseline (*“Considering your current state of health, when do you think you will be able to return to work after your discharge?”*). The SIBAR has a 7-point response scale, with the answer options: *immediately*, *one month*, *three months*, *six months*, *nine months*, *one year or later*, and *not at all anymore*. As has been done before [90], the single SIBAR-item responses will be dichotomised into a’positive RTW expectation (≤ 3 months)’ and’negative RTW expectation (> 3 months)’.

***Social support*** will be measured with the brief version of the Perceived Social Support Questionnaire (F-SozU K-6) [91]. The F-SozU K-6 has a 5-point response scale, ranging from 1 (*not true at all*) to 5 (*very true*). The sum score ranges from 6 to 30, with higher scores indicating higher levels of general perceived social support.

***Socio-demographics*** will be assessed at baseline (T0) with several items including information on *gender*, *age, education, marital status, cohabitation, residence, total number of inhabitants of the place of residence* (extra item asking for the *number of inhabitants younger than 14 years*) [92], *occupational status, company sector, monthly gross household income* [73]*, degree of disability* [89]*, ethnicity, migration* [93] and *distance to the practice of the respective therapist or other practitioners* [73]. Data on *household income* will be collected at all five measurement points for the health-economic evaluation.

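### The adjusted primary model picks socio-demographic covariates by chance imbalance between arms, and neither it nor the unadjusted model is named as the test of RQ I

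*Protocol article*

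**What the plan says.** Under Statistical analyses, Effectiveness evaluation, the protocol article sets out the primary analysis in steps.

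- General method: "The primary outcome will be analysed using a logistic regression model to determine the odds ratio of the intervention effect".
- Step 1, no covariates: "First, we will estimate a baseline model including treatment group (IG vs. CG) as a dummy-coded predictor variable and SRTW achievement as the outcome variable".
- Step 2, centre always included: "Second, we will compute an adjusted estimate by including the stratification variable of the study centres". The same sentence then adds a conditional part: "if necessary, other socio-demographic variables for which differences between IG and CG occurred despite randomisation".
- Step 3, exploratory: "Third, we will explore interaction effects between treatment group and all baseline assessments of the secondary outcomes and further variables".
- Test level: "In these and subsequent models, we will adopt a significance level of 5% for testing the focal parameters".

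No criterion is given for what counts as a difference or for when adjustment becomes necessary. Neither the step 1 nor the step 2 estimate is designated as the answer to RQ I.

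Three other places bear on the point. Allocation and blinding says that randomisation was stratified by study centre and that the evaluators are not blinded. Further variables, which covers RTW expectation and the socio-demographic items among others, gives their role as follows: "The following variables will be predominantly used as possible outcomes, covariates, moderators, or mediators within further exploratory analyses". The end of the statistical section leaves further details to an analysis plan, to be pre-registered before database closure.

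**The concern.** Four things are unsatisfactory in the stated rule.

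1. **It selects on the wrong property.** With concealed 1:1 randomisation, a baseline difference between arms is a chance event. A covariate is worth including because it predicts the outcome, and the size of an imbalance does not show that.
2. **It leaves the covariate set open.** The wording requires a look at balance by arm and a judgement about necessity, made by evaluators who know the allocation. Because odds ratios are non-collapsible, the quantity being estimated changes with the set chosen.
3. **It reaches only socio-demographic variables.** RTW expectation, RTW self-efficacy, work ability and the BSI-18 are all measured at baseline. They are plausible predictors of SRTW, but the rule keeps them out of the main-effect primary estimate.
4. **Two estimates stand side by side.** One omits the stratification factor and the other includes it. Both are tested at 5%, and the article does not say which one decides.

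At stake are a clear answer to RQ I and some power from data already being collected.

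**Working it through.** **Inputs from the protocol article.** SRTW 60% under CAU against 75% under RTW-PIA, power 80%, significance level 5%, 152 per arm, 40% drop-out, 506 in total (Sample size and power calculation). Five centres, with stratification by centre (Study setting; Allocation and blinding). The socio-demographic list under Further variables has 14 items, or 15 with the extra question on inhabitants under 14 years.

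**Assumptions, not in the documents.** A two-sided test; a difference means p<0.05; independent candidate items; the prognostic strengths stated below.

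**Step 1: reproduce the plan's figure.** Two-proportion formula with pooled variance under the null, mean rate 0.675:

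n = [1.960 × √(2 × 0.675 × 0.325) + 0.842 × √(0.60 × 0.40 + 0.75 × 0.25)]² / 0.15² = [1.298 + 0.550]² / 0.0225 ≈ 152 per arm.

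The stated figure reproduces. The total is 304 / 0.6 = 506.7, stated as 506. This is an unadjusted comparison, with odds ratio (0.75/0.25)/(0.60/0.40) = 2.00.

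**Step 2: how often the rule would fire by chance.** P(at least one flag) = 1 − 0.95^k:

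| k items | Probability |
|---|---|
| 13 | 49% |
| 14 | 51% |
| 15 | 54% |

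Under these assumptions, whether the second model contains anything beyond arm and centre is close to a coin toss.

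**Step 3: simulation of the competing models.** There were 4,000 trials per scenario, each with 304 evaluable participants, five centres balanced within centre and no centre effect. Of 13 independent standard-normal covariates, three are prognostic, each with log-odds 0.3 or 0.5 per SD. Marginal rates are 60% vs 60% or 60% vs 75%. Monte Carlo standard error is √(0.05 × 0.95/4000) = 0.3 points near 5% and √(0.8 × 0.2/4000) = 0.6 points near 80%.

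| Quantity | Log-odds 0.3 | Log-odds 0.5 |
|---|---|---|
| Type I error, unadjusted | 4.1% | 4.6% |
| Type I error, imbalance rule | 4.5% | 4.6% |
| Type I error, fixed prognostic set | 4.6% | 5.4% |
| Type I error, unadjusted or imbalance rule significant | 4.8% | 5.4% |
| Unadjusted and imbalance-rule tests disagree, no effect | 1.0% | 1.6% |
| Unadjusted and imbalance-rule tests disagree, 60% vs 75% | 2.5% | 3.3% |
| Power, unadjusted | 80.0% | 80.1% |
| Power, imbalance rule | 79.8% | 80.6% |
| Power, fixed prognostic set | 82.0% | 85.0% |
| Average odds ratio, unadjusted | 2.02 | 2.02 |
| Average odds ratio, imbalance rule | 2.05 | 2.05 |
| Average odds ratio, fixed prognostic set | 2.13 | 2.29 |

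The simulation is generous to the imbalance rule in one respect: the three prognostic covariates are in the pool from which it selects, whereas the protocol's clinical baseline variables are outside that pool.

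**Step 4: cross-check.** A separate simulation (3,000 trials per setting, 152 per arm) adjusted for one prognostic score with log-odds 0.5, 0.8 or 1.0 per SD. Power rose from 79.9% to 81.9%, from 80.3% to 85.2% and from 78.8% to 85.2%. The first two settings are close in strength to three covariates at 0.3 (0.3 × √3 = 0.52) and at 0.5 (0.5 × √3 = 0.87), and the gains agree.

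**The case against.** The strongest reply is that an article may leave the choice of primary model, and the meaning of a difference, to the analysis plan, which is not shown. The models are also given in an order, and the sample size matches the unadjusted one. This has weight for the missing designation: the unseen plan may name a primary model. It does not answer the covariate rule, which the article states rather than defers. A plan that only adds details would carry that rule forward. The plan is due before database closure, so balance by arm could be known before the covariates are fixed.

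Several stronger readings are tempting but not supported.

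- *Centre is ignored.* It is missing only from step 1. It is unconditional in step 2, where only the socio-demographic part is data-driven.
- *The prognostic baseline data are never used.* They enter the exploratory interaction models. Any that predict missingness enter the estimation through multiple imputation, and diagnosis groups have a sensitivity analysis. The loss concerns the main-effect primary estimate only.
- *The false-positive rate is inflated.* The simulation does not show this to any material degree.
- *The shift in the odds ratio is itself the harm.* Fixed prognostic adjustment moves it further (2.13 to 2.29) than the imbalance rule does (2.05). The defensible complaint is that the target is not fixed in advance.

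The numbers also have limits that stand. The p<0.05 criterion is not in the protocol. Independence is unlikely, for example for marital status and cohabitation. The documents give no prognostic strength. The simulation uses complete data, whereas the plan uses multiple imputation.

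**Conclusion.** The point holds in a limited form. The article fixes a poor covariate rule, selection by observed imbalance among socio-demographic variables, and sets it beside an unadjusted model that omits the stratification factor, without saying which result answers RQ I. The main cost is ambiguity and avoidable discretion for unblinded evaluators.

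The measurable harm is modest. Type I error stays near 5%, and the two tests disagree in roughly 1% to 3% of trials. About 2 to 5 points of power are forgone, if the baseline variables are as prognostic as assumed. The 49% to 54% chance of at least one flagged item is illustrative and rests on the assumed p<0.05 criterion and independence. A reader might infer that the primary result would be invalid or the sample size wrong. Neither follows: an unadjusted or a centre-adjusted logistic model would be a valid primary analysis if named, and 152 per arm is unaffected.

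**What to change.** In the analysis plan, before outcome data or balance by arm are seen:

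1. Name one primary model for RQ I: logistic regression on arm, centre and a short fixed list of prognostic baseline variables already collected. Candidates are RTW expectation, RTW self-efficacy, the Work Ability Score and the BSI-18 index. The exact list is for the trial team to choose.
2. Delete the rule that adds socio-demographic variables on observed difference.
3. Keep the unadjusted model and label it supportive.
4. Optionally, report a standardised risk difference beside the odds ratio, since the sample size is set on 60% against 75%.

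The minimum repair is to name one model and remove the imbalance clause; prognostic adjustment is an added gain in efficiency. The cost is a few sentences. No new data are needed and the sample size does not change.
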